## Abstract

**Introduction::**

Endoscopic ultrasound-guided hepaticogastrostomy (EUS-HGS) is a novel drainage option for patients with an inaccessible papilla. Although EUS-HGS has clinical benefits in patients for whom endoscopic retrograde cholangiopancreatography (ERCP) has failed, the rates of adverse events (AEs) associated with EUS-HGS, such as bile peritonitis and stent migration, are higher than for other procedures. The development of a dedicated system for EUS-HGS is therefore desirable to reduce the rate of AEs. We developed a dedicated system for EUS-HGS (HG01 system) which is composed of a 19-gauge needle, 0.025-inch guidewire, a thin delivery system for tract dilation, and an antimigration metal stent. This study is designed to evaluate the efficacy and safety of EUS-HGS using the HG01 system in malignant biliary obstruction.

**Methods/design::**

This is a single-arm multicenter prospective study involving 40 patients across six tertiary centers in Japan. Patients with an unresectable malignant biliary obstruction in whom biliary drainage with ERCP failed, is not possible, or is very difficult will be registered in the study. The primary endpoint is the clinical success rate. The secondary endpoints are the technical success rate, procedure-related AE rate, procedure time, procedure success rate using only the HG01 system, stent patency rate, re-intervention success rate, re-intervention method, survival rate, and distance of movement of the stent position.

**Discussion::**

We expect use of the HG01 system to reduce the rate of AEs during EUS-HGS, especially bile leakage and stent migration. If the efficacy and safety of EUS-HGS using the HG01 system is confirmed in the present study, it is likely to be considered the first-choice device for use during EUS-HGS.

## Introduction

1

Endoscopic ultrasound-guided biliary drainage (EUS-BD) was first reported in 2001^[1]^ and is considered to be an effective drainage method for patients with bile duct obstruction for whom biliary drainage by endoscopic retrograde cholangiopancreatography (ERCP) is unsuccessful or difficult.^[2–4]^ Compared with percutaneous transhepatic biliary drainage, which has been used when ERCP is unsuccessful, EUS-BD can be performed as an internal drainage method and has a higher technical success rate (100% vs 86.4%, *P* < .007) and lower adverse event (AE) rate (18.2% vs 70.6%, *P* < .001).^[5]^ We previously conducted a multicenter prospective clinical study to evaluate the efficacy and safety of EUS-BD using a metal stent for ERCP and reported on its efficacy and safety.^[6,7]^ Moreover, compared with conventional drainage under ERCP, EUS-BD is expected to have a longer patency period because the stent is not located within the tumor.^[8]^

EUS-BD can be categorized into two main types: EUS-guided hepaticogastrostomy (EUS-HGS), which creates an anastomosis between the stomach and the intrahepatic bile duct, and EUS-guided choledochoduodenostomy (EUS-CDS), which creates an anastomosis between the duodenal bulb and the extrahepatic bile duct. EUS-CDS can be indicated in patients with distal biliary obstruction and normal gastrointestinal structures, whereas EUS-HGS is more widely indicated in patients who have hilar biliary obstruction and/or surgical reconstruction. However, the rates of AEs associated with EUS-HGS, such as bile peritonitis and stent migration, are higher than for EUS-CDS.^[9]^ One of the reasons for the high rate of AEs associated with EUS-HGS is that no dedicated devices are available for EUS-HGS, with devices and metal stents designed for ERCP being used instead. EUS-HGS using these devices and metal stent has been reported to be associated with bile peritonitis due to stent migration.^[10]^ In addition, the leakage of bile during fistula dilation step also causes postprocedural bile peritonitis.^[11,12]^ The development of a dedicated antimigration metal stent with a thin delivery system for tract dilatation for EUS-HGS is therefore desirable to reduce the rate of AEs.

We thus developed a partially covered self-expandable metal stent with a thin delivery system (7.2F) dedicated to EUS-HGS and reported on the efficacy and safety of EUS-HGS in experimental settings.^[13]^ It is expected that EUS-HGS with the dedicated delivery system will reduce bile leakage by eliminating the dilation step and the dedicated stent with laser-cut wire and anchoring hooks may help to prevent stent migration. Moreover, we also developed other dedicated devices specific to EUS-HGS such as a 19-gauge needle and 0.025-inch guidewire. This single-arm multicenter study aims to evaluate the efficacy and safety of EUS-HGS using the dedicated system (HG01 system) in patients with malignant biliary obstruction after failed ERCP.

## Methods/design

2

### Ethical approval and patient consent

2.1

This study was approved by the Wakayama Medical University Hospital Institutional Review Board (number: 1-02021A) and, subsequently, by the institutional review boards of all other participating centers. All patients will provide written informed consent. The trial is registered with the Japan Registry of Clinical Trials (JRCT; trial registration: jRCT2052210020).

### Study aims and design

2.2

This is a single-arm multicenter study across six tertiary centers in Japan that aims to evaluate the efficacy and safety of a system for endoscopic ultrasound-guided hepaticogastrostomy (HG01) in 40 patients with malignant biliary obstruction. The first three patients will be performed at the main institution, Wakayama Medical University. An interim analysis of safety will be performed after the procedure is completed on the first three patients, and the Data and Safety Monitoring Committee (DSMC) will evaluate the safety of the system and decide whether the trial can be continued afterwards. If the DSMC decides that the system is safe enough to continue the trial, the trial will be conducted in the remaining 37 patients at all participating institutions.

### Patients

2.3

At each center, the on-site study investigators will obtain informed consent from the candidates, input necessary information into an electronic data capture system, confirm that the candidates meet the eligibility criteria (i.e., the candidates meet all the inclusion criteria and none of the exclusion criteria), and register the candidates with the registration secretariat. After confirming that a candidate meets the criteria, a registration number will be issued, and the registration will be considered complete.

### Inclusion criteria

2.4

The following inclusion criteria will be applied.

(1)Age of more than 20 years when providing informed consent.(2)Pathological diagnosis of malignancy.(3)Biliary obstruction due to unresectable malignant tumor.(4)Biliary drainage with ERCP failed, was not possible, or was considered difficult.(5)Serum bilirubin level of higher than 3.0 mg/dL before enrollment.(6)Informed consent document obtained from the patient.

### Exclusion criteria

2.5

The following exclusion criteria will be applied.

(1)Impossible to perform endoscopy.(2)Total gastrectomy has already been performed.(3)Left hepatectomy has already been performed.(4)Bismuth classification for hilar biliary carcinoma: Type IIIb or Type IV.(5)Liver cirrhosis.(6)Ascites around the liver on CT.(7)With percutaneous trans-hepatic biliary drainage (PTBD) tube at time of obtaining informed consent.(8)Planned insertion of a metal stent in the upper gastrointestinal tract within 7 days before treatment.(9)Performance status 4.(10)Other severe diseases of the heart, lung, kidney, and/or liver of ASA 4 or higher.(11)Poor general condition and estimated prognosis of less than 2 months.(12)Hemorrhagic diathesis including fatal aneurisms or severe coagulation disorder.(13)Participation in other clinical trials (except in a non-intervention arm).(14)Women who may possibly be pregnant or who want to be pregnant.(15)Metal allergy to nickel-titanium.(16)Known allergy to iodine contrast agents.(17)Patients whom the investigators otherwise decide are inappropriate to participate in the trial.

### HG01 system

2.6

The HG01 system is composed of a 19-gauge needle, 0.025-inch guidewire, delivery system, and metal stent. The needle is used to puncture and access the intrahepatic bile duct from the stomach under echoendoscopy and allows simultaneous insertion of the guidewire with injection of the contrast agent (Fig. 1A). The tip of the guidewire is made of a platinum-iridium metal coil without resin coating, which is less likely to shear because of contact with the needle tip (Fig. 1B). However, this guidewire cannot be used with electrocautery catheter due to its high electric conduction. The delivery system has a diameter of 7.2F and a soft tip that is tapered, which facilitates its insertion into the intrahepatic bile duct without fistula dilation. In experimental settings, the delivery system can be inserted into the bile duct without fistulous tract dilation^[13]^ (Fig. 1C). The design of the stent may prevent stent migration because it is equipped with the partially covered laser-cut structure and antimigration anchoring hooks^[13]^ (Fig. 1D).

**Figure 1 F1:**
[figure not shown]
The dedicated system for EUS-HGS (HG01 system). (A) The 19-gauge needle is used to puncture and access the intrahepatic bile duct from the stomach under echoendoscopy and allows insertion of the guidewire with simultaneous injection of the contrast agent. (B) The tip of the guidewire is made of a metal coil, which is less likely to shear because of contact with the needle tip. (C) The diameter of the delivery system is 7.2F, and its tip is soft and tapered. (D) The stent is 8 mm in diameter and 100 mm long. It is made from laser-cut nitinol wire and is partially covered by a polyurethane membrane. The distal 10 mm of the stent is uncovered, and hooks are attached to the proximal end to prevent distal stent migration.

### Procedure

2.7

An echoendoscope is inserted orally and advanced to the stomach. An appropriate target intrahepatic bile duct is then confirmed with EUS from the stomach, and Doppler imaging is used to rule out any intervening vessels. The 19-gauge dedicated needle is then used to puncture the intrahepatic bile duct under endosonographic guidance. After the bile juice is aspirated, contrast medium is injected, and the 0.025-inch dedicated guidewire is advanced into the intrahepatic bile duct. If the guidewire does not reach the downstream part of the bile duct with a long distance sufficient for metallic stent placement, a catheter or another guidewire will be used to reach the bile duct site. Thereafter, an attempt is made to insert the dedicated delivery system via the fistula without using any dilation devices. If this is successful, the dedicated metal stent is expanded between the intrahepatic bile duct and the stomach under EUS and fluoroscopic guidance. If it is difficult to advance the delivery system via the fistula, the fistulous tract is dilated using dilation devices.

### Primary endpoint

2.8

The primary endpoint is the clinical success rate, which is defined as follows:

(1)Improvement in the serum total bilirubin (T-Bil) level to below 50% of the highest pretreatment level on at least two of four measuring points including days 3, 7, 14, and 21.(2)A decrease in the T-Bil level after treatment compared with the highest pretreatment T-Bil level, and a decrease in the diameter of the bile duct by 50% or more on day 14 on computed tomography (CT) imaging compared with the largest pretreatment diameter of the bile duct.

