### Secondary endpoints

2.9

The secondary endpoints are as follows:

(1)Technical success rateTechnical success is defined as the stent being positioned between the stomach and intrahepatic bile duct, as seen on CT performed 1 day after treatment.(2)Procedure-related adverse event (AE) rateProcedure-related AEs are defined as AEs judged to be “related,” “possibly related,” or “might be related” to the procedure. Procedure-related AEs will be divided into early AEs occurring within 14 days after treatment and late AEs occurring from 15 to 60 days after treatment. Early AEs may include postprocedural pancreatitis, cholangitis, stent migration, stent deviation, gastric ulcer associated with mechanical irritation of the stent, bleeding, gastrointestinal injury, and procedure-related deaths. Late AEs may include stent migration, stent deviation, stent occlusion, and gastric ulcer associated with mechanical irritation from the stent.(3)Procedure timeProcedure time is defined as the time from the puncture of the bile duct to stent placement.(4)Procedure success rate using only the HG01 systemProcedure success using only the HG01 system is defined as successful insertion of the stent into the left intrahepatic bile duct using only the HG01 system.(5)Stent patency rate at 30 and 60 days after treatmentThe stent patency rates are defined as the percentage of patients who do not experience stent dysfunction from the date of stent insertion to 30 and 60 days after treatment.Stent dysfunction is defined as follows.(1)A T-Bil level of ≥3.0 mg/dL when the lowest T-Bil level measured after treatment is <1.5 mg/dL.(2)A T-Bil level more than 2.0 times the lowest level when the lowest T-Bil level measured after treatment is more than 1.5 mg/dL.(6)Re-intervention success rate and re-intervention methodRe-intervention success is defined as the placement of a new drainage tube and improvement in the T-Bil level to below 50% of the highest pretreatment level within 21 days after re-intervention.The following re-intervention methods can be selected.(1)Treatment from the stent(2)Other EUS-guided biliary drainage(3)Trans-papillary biliary drainage(4)Percutaneous transhepatic biliary drainage(5)Surgical cholangiojejunostomy(7)Survival rate at 60 days after treatment(8)Distance of movement of the stent position at 1, 14, 30, and 60 days after treatmentThe length of the stent inside the stomach on the abdominal CT at day 0 after treatment will be compared with the length of the stent inside the stomach on days 1, 14, 30, and 60 after treatment, to evaluate the distance of movement of the stent from its placement position.

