#### Sample size calculation

2.12.1

In a meta-analysis on EUS-BD, the median rate of clinically effective improvement in 26 articles enrolling more than ten patients was 88.0%, and the median of 3 articles enrolling more than 100 patients was 89.5%.^[3]^ In addition, the median rate of clinically effective improvement in a randomized controlled trial was 87.5%.^[16]^ On the basis of these reports, we set the expected clinical response rate for this study to 88%. In the meta-analysis,^[3]^ the 5% point improvement in clinical efficacy of the 26 articles with more than ten cases was 72.5%. Therefore, we set the threshold for the clinically effective improvement rate to 73%. In this case, the minimum number of patients required to achieve a power of 80% or higher at the significance level of α-0.05 is 37 patients. We set the target number of patients to 40, assuming that a small number (about 10%) of patients will drop out of the study.

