#### Statistical analysis

2.12.2

In the effectiveness analysis for the population, the full analysis set (FAS) is the main analysis, and the per protocol analysis set (PPS) acts as a reference. In the safety analysis for the target population, all test examples will be analyzed. For the clinical success rate, a test of the mother ratio against the threshold clinical success rate of 0.73 will be performed for the FAS. The exact method will be used to calculate the *P*-value, and a one-sided test will be performed. If the *P*-value is below the significance level of α = 0.05, EUS-HGS using the HG01 system will be considered effective. For the rates of technical success, procedure-related AE, successful procedures using only the HG01 system, and stent patency at 30 days, the percentages and 95% Clopper–Pearson confidence intervals will be calculated. For the procedure time, the mean and 95% confidence interval will be calculated. For the overall survival time, the survival rate will be estimated using the Kaplan–Meier method, and the 95% confidence interval at each time point will be calculated using Greenwood's formula. In addition, a Kaplan–Meier plot will be used to draw the survival curve. For the distance of movement of the stent position at 1, 14, 30, and 60 days after treatment, the mean and 95% confidence interval will be calculated. We will also create transition charts for each case and for the mean values. Error bars representing standard error will be added to the mean trend chart. The number and percentage of AEs will be calculated for each grade of AEs. All analyses will be performed using R version 4.1.2 (The R Foundation for Statistical Computing, Vienna, Austria).

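### As worded, the primary endpoint can score a patient drained by another route as an HG01 clinical success; the possible bias is upward only, and its size is not given

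*Protocol article*

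**What the plan says.** Section 2.8 gives two criteria for clinical success. The first is total bilirubin (T-Bil) "below 50% of the highest pretreatment level on at least two of four measuring points including days 3, 7, 14, and 21". The second is any T-Bil fall from the pretreatment peak together with "a decrease in the diameter of the bile duct by 50% or more on day 14 on computed tomography (CT) imaging". No word joins the two; they read most naturally as alternatives. Neither mentions the stent or any other drainage.

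Stent placement appears separately, as technical success in 2.9(1), judged on day 1 CT. It is not a condition of clinical success.

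On re-intervention, 2.9(6) states: "The following re-intervention methods can be selected". The list covers treatment through the existing stent, other EUS-guided drainage, and transpapillary, percutaneous and surgical drainage. No earliest day is given. Success of a re-intervention means a new drainage tube and "improvement in the T-Bil level to below 50% of the highest pretreatment level within 21 days after re-intervention".

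Section 2.12.2 tests the clinical success rate in the full analysis set (FAS) against 0.73 with an exact one-sided test. A significant result is read as showing that EUS-HGS with the HG01 system is effective.

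**The concern.** The conclusion is about a device, but the endpoint as written records whether the patient was drained, by whatever route. Suppose placement fails on day 0, or the stent migrates in the first week, and the patient is drained percutaneously. If T-Bil is below half the pretreatment peak on days 14 and 21, criterion 1 is met. If the duct has shrunk by half on day 14 and T-Bil has fallen, criterion 2 is met. The same bilirubin fall could also count as a re-intervention success under 2.9(6).

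The article itself makes the situation plausible. It names stent migration and deviation as early adverse events (2.9(2)) and cites 95% technical success for EUS-HGS (Discussion). It also excludes patients with a percutaneous drain at consent (2.5), so competing drainage is guarded against at baseline but not afterwards. With a fixed threshold and no control arm, any miscredit goes straight into the estimate and the decision.

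**Working it through.** **Inputs.** Threshold 0.73, expected rate 0.88, minimum 37 and target 40 patients (2.12.1); exact one-sided test at 0.05 (2.12.2); 95% technical success, 23% procedure-related adverse events, stent migration 13% (Discussion). The share *f* of true HG01 failures that are drained by another route in time and credited is not in the documents. It is an assumption, shown as a range.

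**The plan's own figure.** The stated minimum "to achieve a power of 80% or higher at the significance level of α-0.05 is 37 patients". It reproduces with a normal approximation, variance at 0.88 and two-sided 0.05: (1.960 + 0.842)² × 0.88 × 0.12 / 0.15² = 36.84, rounded up to 37. That is not the exact one-sided test of 2.12.2. The mismatch is a separate matter, but it bears on power under the fix.

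**Decision rule.** At N = 40 and rate 0.73, P(X ≥ 35) = 0.0235 and P(X ≥ 34) = 0.057. So 35 successes are needed and the actual size is 0.0235. One patient can decide the result: 34/40 is not significant and 35/40 is. At N = 37 the rule is 32 or more, with size 0.0417.

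**Effect of credited failures.** If the true HG01-attributable rate is 0.73, the rate the endpoint measures is q = 0.73 + 0.27*f*. The chance of declaring the system effective is P(X ≥ 35 | 40, q), or P(X ≥ 32 | 37, q):

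| *f* | q | N = 40 | N = 37 |
|---|---|---|---|
| 0% | 0.730 | 0.0235 | 0.042 |
| 5% | 0.7435 | 0.036 | 0.060 |
| 10% | 0.757 | 0.053 | 0.085 |
| 20% | 0.784 | 0.110 | 0.159 |
| 30% | 0.811 | 0.207 | 0.275 |

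**Break-even.** At N = 40 the probability reaches 0.05 at q = 0.755, that is 2.5 points above 0.73. This is 40 × 0.025 = 1 patient, or about 9.3% of failures. At N = 37 it takes 0.7 points.

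**Anchoring the range.** The cited 95% technical success leaves 5% without a stent, or 2 of 40. If all of these were drained elsewhere and credited, q = 0.78 and the probability is 0.099 at N = 40 (0.146 at N = 37). The adverse event percentages listed in the Discussion add up to 13 + 17 + 13 + 17 + 10 + 2 + 7 + 21 = 100, so they read as shares of events. Migration is then about 0.23 × 0.13 = 3% of patients. The two mechanisms together give about 8 points, and 8/27 is about 30% of failures. The last row of the table is therefore roughly a ceiling for what these citations could support. It needs every such patient to be re-drained and to respond in time.

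**Timing.** For criterion 1, the other drainage must bring T-Bil below half the peak by day 14 and keep it there on day 21 at the latest. For criterion 2, it must act on the duct by day 14. Later re-interventions cannot be credited.

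**The case against.** No sentence says that rescued patients count as successes. This is a condensed article, and FAS membership and the handling of later events may be set out in documents not shown. Re-intervention has its own endpoint, which suggests the sponsor thinks of it as a separate outcome. If both criteria in 2.8 were required, a rescued patient would also need the duct shrinkage on day 14. The 73% and 88% come from published rates whose success definitions the article does not give. If those also count rescued patients, the bias against the threshold is smaller, and tightening only this trial's definition would create a mismatch.

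Most of this stands as a limit on size and certainty. It does not remove the point. Section 2.8 states a complete scoring rule, and followed literally that rule admits these patients. A separate re-intervention endpoint does not take them out of the primary one. Requiring both criteria would narrow the route without closing it.

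A reader might go further and infer that the trial's type I error is inflated. The documents do not support that: for the endpoint as written, the exact test keeps its size of 0.0235 at N = 40. The excess arises only against the HG01-attributable rate, and only if enough failures are credited. A reader might also picture half of all failures being rescued, which would give 0.541. That needs 0.5 × 27 = 13.5 credited points, well beyond the roughly 8 points that the cited figures could support.

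**Conclusion.** The definition in 2.8 permits credit for drainage that HG01 did not provide, and any such credit can only raise the tested rate. Whether it would change the result is not known, because the documents give no rate of early re-intervention. At N = 40 and a true HG01-attributable rate of 73%, the chance of a wrong device claim stays below 0.05 until about one patient is credited. It is about 0.10 if all of the cited 5% technical failures are credited, and about 0.21 at 30% of failures. These figures assume that 40 patients are analysed, that criteria 1 and 2 are alternatives, and that the literature threshold refers to drainage by the procedure itself. The point is worth settling because one patient can decide the test and the remedy is a single sentence.

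**What to change.** Add to 2.8: *For scoring the primary endpoint, a patient without a placed HG01 stent, or who receives biliary drainage by a route other than the HG01 stent before the criterion is met, counts as a clinical failure.* Report the rate without this condition as a supplementary result. State in advance how re-treatment through the existing stent, the first method in 2.9(6), is scored, since the HG01 stent may still be the route of drainage. Say whether criteria 1 and 2 are alternatives. If a scoring rule already stands in another trial document, carry it into 2.8. Settle this before outcome data are examined.

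This is a scoring rule only; it changes nothing about who is re-drained, when or how. The data are already needed: placement for 2.9(1), and the date and method of re-intervention for 2.9(6).

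The cost is a possibly lower observed rate and lower power. With the exact one-sided test at N = 40, power is 65.4% at a rate of 88%. If the 88% includes rescued patients and the attributable rate is, for example, 85%, it is about 43%. Section 2.12.1 should therefore say whether the literature rates behind 73% and 88% use a comparable definition of success.
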